**Supplementary Figure 1. NIBIT-M4 cohort.**

Overview of sample profiling and clinical information for N=14 patients of NIBIT-M4 trial.

[figure not shown]

**Supplementary Figure 2. Evaluation of the methylation pattern for lesions harboring mutation in chromatin organization (*DNMT1* or *SETD2*).**

**a** Global Methylation pattern as function of the time of biopsy in genomics regions for *DNMT1* and *SETD2* mutant and wild-type lesions. The increasing (green) or decreasing (red) trend was evaluated based on the inclination of the robust linear regression line between the three time points (mutant patients  $n=3$ , wild-type patients  $n=11$ ). **b** Regulatory regions (mutant patients  $n = 3$ , wild-type patients  $n = 11$ ). **c** Classes of long terminal repeat (LTR) (mutant patients  $n = 3$ , wild-type patients  $n = 11$ ). **d** Correlation between expression and methylation of LTR in mutant and wild-type cases (Spearman's correlation coefficient ( $r$ ) and associated  $p$ -values from two-tailed correlation test). Lines represent robust least squares linear regression. In **a**, **b**, **c**, and **d**, bands represent confidence intervals ( $\pm 0.95$ ) around a linear model fitted by robust regression using an M estimator. Source data are provided as a Source Data file.

[figure not shown][figure not shown]

**Supplementary Figure 3.** *Mutational signature analysis for patients with available matched normal.*

Deconvolution of the mutational patterns on COSMIC collection of mutational signatures v3.2. Source data are provided as a Source Data file.

a

[figure not shown]

b

[figure not shown]

c

[figure not shown]

**Supplementary Figure 4. Biomarkers and functional characterization of NIBIT-M4 trial.**

**a** ICI response prediction scores between R (n = 18) and NR (n = 23) samples at all time points ( $p$ -value from two-sided Student's  $t$ -Test). Box plots show the median as center, the lower and upper hinges that correspond to the 25th and the 75th percentile, and whiskers that extend to the smallest and largest value no more than  $1.5 \times \text{IQR}$ . Values that stray more than  $1.5 \times \text{IQR}$  upwards or downwards from the whiskers are considered potential outliers and represented with dots. **b** Heatmap of enrichment  $z$ -scores (from NANOSTRING gene expression assay) computed for selected pathways between R (n = 18) and NR (n = 22) samples grouped for treatment timepoints. Symbols within squares represent significance levels for each treatment timepoint ( $p$ -value from two-sided Student's  $t$ -Test: \*:  $p < 0.05$ , \*\*:  $p < 0.01$ , \*\*\*:  $p < 0.001$ ). **c** Dot plot of enriched canonical pathways from Ingenuity Pathway Analysis (IPA) using significant differentially expressed genes between R (n = 18) vs NR (n = 23) samples at all time points ( $\text{FDR} < 0.1$ , from glmLRT as implemented in EdgeR^12) as input. x axis represents the  $-\log(p\text{-value})$  from right-tailed Fisher exact test. Source data are provided as a Source Data file.

**a**[figure not shown]**b****week0**[figure not shown]**week4**[figure not shown]**week12**[figure not shown][figure not shown]

**Supplementary Figure 6.** *Evaluation of the methylation pattern for R and NR lesions.*

**a** Global Methylation pattern as function of the time of biopsy in genomics and regulatory regions for R (n = 18) and NR (n = 23) lesions. The increasing (green) or decreasing (red) trend was evaluated based on the inclination of the robust linear regression line between the three time points. Bands represent confidence intervals ( $\pm 0.95$ ) around a linear model fitted by robust regression using an M estimator. **b** Starburst plot of hyper-methylated and down-regulated genes (lower-left quadrant), and hypo-methylated and up-regulated genes (upper-right quadrant) between R (n = 6) and NR (n = 8) patients at different weeks of treatment (left). x and y axis represent the  $-\log(p\text{-value})$  multiplied by the sign of the difference from the differential methylation (from linear model, as implemented in the limma package) and expression analyses (from glmLRT, as implemented in EdgeR^12), respectively (left). Heatmap of enrichment scores as  $-\log_{10}(p\text{-value})$  from GO:BP over-representation analysis (as implemented in SMITE package) for hypo-methylated and up-regulated genes between R (n = 6) and NR (n = 8) patients at different weeks of treatment (right). Source data are provided as a Source Data file.

**a**

[figure not shown]

**b**

[figure not shown]

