**Supplementary Figure 8. GIE at baseline of treatment in NIBIT-M4 trial.**

**a** Boxplot of Genetic Immunoediting (GIE) score at baseline (left,  $p$ -value of two-sided Student's t-Test) and all time points (right,  $p$ -value of two-way Mixed-model ANOVA, within-subjects factor: time of treatments; between-subjects factor: response) between R and NR patients. **b** Scatterplot of ICR score by GIE for R ( $n = 6$ ) and NR ( $n = 8$ ) patients at baseline (left) and their proportion (right) after classification as ICR/GIE classes ( $p$ -value from two-sided Pearson's chi-squared test statistic). Source data are provided as a Source Data file.

**a**[figure not shown]**b**[figure not shown]

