### **6.3.8 Tumor Tissue biopsy**

Tumor tissue biopsy of cutaneous/subcutaneous lesions of at least 5 mm diameter will be performed for each subject at baseline, W4 and W12 as outlined in Table 6.1.

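### Supplementary Figure 4a tests 41 serial biopsies from 14 patients as if they were independent, so the error rate of its pooled responder comparison is not controlled

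*Combined protocol and SAP*

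**What the plan says.** Supplementary Figure 1 describes the profiled cohort: "Overview of sample profiling and clinical information for N=14 patients of NIBIT-M4 trial". Supplementary Figure 6b gives the split by response as "R (n = 6) and NR (n = 8) patients at different weeks of treatment". Protocol Section 6.3.8 states that tumour biopsy "performed for each subject at baseline, W4 and W12".

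Three panels compare responders (R) with non-responders (NR) in different ways:

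- Figure 4a reports "ICI response prediction scores between R (n = 18) and NR (n = 23) samples at all time points", with a two-sided Student's t-test.
- Figure 4b, in the same caption, tests pathway scores separately at each treatment time point. Its sample totals are 18 and 22.
- Figure 4c runs a pathway analysis "using significant differentially expressed genes between R (n = 18) vs NR (n = 23) samples at all time points", selected by the edgeR likelihood-ratio test at FDR below 0.1.

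For the comparison over all time points in Supplementary Figure 8a, the p-value is "of two-way Mixed-model ANOVA, within-subjects factor: time of treatments; between-subjects factor: response".

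Section 8.3.3 calls the translational work exploratory and plans no formal tests. Appendix A lists assays and a general aim of correlating results with clinical parameters. Neither specifies an R versus NR test or says how serial samples are to be handled.

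**The concern.** Response does not vary between a patient's biopsies, so the R versus NR contrast rests on 14 independent units. The two-sample t-test in Figure 4a takes its variance and its 39 degrees of freedom (18 + 23 - 2) from 41 samples. If biopsies from one patient resemble each other, the true variance of the difference in means is larger than the test assumes, and the p-values are too small. The hypothesis of no R versus NR difference is sound. The distribution against which the statistic is judged is not.

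Figure 8a shows that the supplement treats time as a within-subject factor when it analyses the same kind of comparison for another score. Figure 4a describes no such step. At stake is which response-prediction scores are reported as separating responders from non-responders.

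**Working it through.** **Reproducing the sample counts.** With one biopsy per patient per visit, 6 × 3 = 18 R samples. For NR, 8 × 3 = 24, and one missing sample gives 23. The total is 18 + 23 = 41, as in the caption. The documents do not say which NR sample is missing; I assume a single patient with two samples. They give no p-value, error rate or ICC for this test, so nothing further can be reproduced.

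**Design effect for the difference in means (compound symmetry, total variance 1).**

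Variance assumed by the t-test: 1/18 + 1/23 = 0.0990.

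True variance: ICC × [6×3²/18² + (7×3² + 2²)/23²] + (1 - ICC) × 0.0990. The bracket is 54/324 + 67/529 = 0.1667 + 0.1267 = 0.2933.

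The ratio is DE = 1 + ICC × (0.2933/0.0990 - 1) = 1 + 1.96 × ICC. The effective number of samples is 41/DE. The approximate type I error is 2 × [1 - Φ(1.96/√DE)].

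**Simulation.** 40,000 runs per setting, normal data, no R versus NR difference, 6 × 3 and 8 × 3 - 1 samples, nominal two-sided 5%. The caption gives no threshold for panel a; 5% is assumed.

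| ICC | DE | Effective n | Approx. error | Simulated, 41 samples | Simulated, 14 patient means |
|---|---|---|---|---|---|
| 0 | 1.00 | 41 | 0.050 | 0.051 | 0.049 |
| 0.1 | 1.20 | 34 | 0.073 | 0.074 | 0.051 |
| 0.2 | 1.39 | 29 | 0.097 | 0.097 | 0.048 |
| 0.5 | 1.98 | 21 | 0.164 | 0.174 | 0.050 |
| 0.8 | 2.57 | 16 | 0.221 | 0.244 | 0.051 |

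Serial correlation that decays with time, AR(1) with 0.3, 0.5 and 0.8, gives 0.107, 0.152 and 0.231.

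**Effect of a shared time trend.** A shift over visits common to both groups adds to the pooled within-group variance but almost cancels in the group difference, so it lowers the rejection rate.

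| Shift over the three visits | ICC 0.2 | ICC 0.5 | ICC 0.8 |
|---|---|---|---|
| none | 0.097 | 0.174 | 0.244 |
| -0.5/0/+0.5 SD | 0.075 | 0.137 | 0.201 |
| -1/0/+1 SD | 0.033 | 0.072 | 0.119 |

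The t-test on patient means stays between 0.048 and 0.052 in every setting run.

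**What this does to a p-value (no time trend).** Dividing the 39-df t-value by √DE and referring it to 12 df (14 - 2), a reported p = 0.01 becomes about 0.04, 0.08 or 0.12 at ICC 0.2, 0.5 or 0.8.

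**Single time point, as in Figure 4b.** Each patient contributes one value. A simulated 6 versus 8 t-test rejects in 0.050 of runs, so that panel does not have this problem.

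**The case against.** The strongest reply is that this is a caption in a results supplement. The protocol calls the work exploratory and specifies no such test. That stands as a limit on consequence: the primary and secondary endpoints are untouched, and a reader who infers that Section 8.3.3 or Appendix A planned an invalid test would be wrong. It does not make the p-values in Figure 4a valid.

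A second reply is that pooling is inferred, because the figure is not shown and Figure 4b also gives total counts although it tests each visit separately. Pooling is nevertheless much the likelier reading: the caption sets samples at all time points in panel a against tests per time point in panel b.

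A third reply concerns size, and it is largely right. A reader might infer that the test rejects 2 to 5 times too often. That follows only from an assumed ICC of about 0.2 to 0.8 with no shared trend. The documents give no ICC, and Section 6.3.8 does not say that the same lesion is sampled each time. A time trend is plausible under a hypomethylating drug, and the supplement itself plots trends over the three time points. With the strong trend above, the factor is 0.7 to 2.4, so the test can even be conservative. This does not rescue the analysis: its error rate then depends on two unknown quantities.

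A reader might also extend the inflation to every R versus NR result. The documents do not support that. Figure 4c uses a different test whose design matrix is not given, and a caption's silence does not prove that patient was ignored. Figures 4b and 6b are analysed by time point or week. Nor do the documents show that any particular reported association is false, or that the trial's biomarker conclusions rest on Figure 4a.

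**Conclusion.** Figure 4a is wrong as written: a patient-level contrast is tested with a sample-level reference distribution. The nominal 5% test rejects in about 10% to 24% of cases if the ICC is 0.2 to 0.8 and no time trend is shared, about 7% at ICC 0.1, and about 3% to 12% (ICC 0.2 to 0.8) under a -1/0/+1 SD trend. These rates rest on the assumed ICC, normal data, one missing NR sample and the pooled reading of the caption. That the error rate is uncontrolled, in either direction, does not depend on any one of the assumed ICC values.

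For Figure 4c the point is a request to state the design; no inflation factor is claimed. The consequence is limited to exploratory p-values and gene lists.

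**What to change.** - **Figure 4a:** re-run with the approach of Figure 8a (response between subjects, time within subjects, random patient effect), which also takes the time trend out of the error term. Fit it in a form that accepts the one missing sample. A t-test on the 14 patient means is a simple alternative. Report n as 6 versus 8 patients.
- **Figure 4c:** state the design matrix. If patient was ignored, rebuild the gene list with a within-patient correlation term (for example limma duplicateCorrelation) or on counts aggregated per patient, and repeat the pathway analysis. Fixed patient blocks will not work: response is constant within patient, so they are aliased with it.
- **Figures 4b and 6b:** no change on this account.

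The cost is re-running existing analyses on existing data. The downside is that some nominal associations may no longer be significant.

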**Supplementary Figure 7. Longitudinal Functional Analysis in NIBIT-M4 trial.**

**a** Heatmap displaying the most significant GO:BP terms enriched (from over-representation analysis, as implemented in SMITE package) by the top 100 genes upregulated and hypomethylated at week12 vs week0 in NR (n = 8) patients. **b** Same as in **a** for R (n = 6) patients. Boxes are colored according to the adjusted *p*-values of the enrichment. Terms with an adjusted *p*-value (SCS multiple testing correction implemented in gProfiler) greater than 0.05 were filtered out. Only genes mapping to selected GO:BP terms were displayed.

**a**

[figure not shown]

**b**

[figure not shown]

**Supplementary Figure 8. GIE at baseline of treatment in NIBIT-M4 trial.**

**a** Boxplot of Genetic Immunoediting (GIE) score at baseline (left,  $p$ -value of two-sided Student's t-Test) and all time points (right,  $p$ -value of two-way Mixed-model ANOVA, within-subjects factor: time of treatments; between-subjects factor: response) between R and NR patients. **b** Scatterplot of ICR score by GIE for R ( $n = 6$ ) and NR ( $n = 8$ ) patients at baseline (left) and their proportion (right) after classification as ICR/GIE classes ( $p$ -value from two-sided Pearson's chi-squared test statistic). Source data are provided as a Source Data file.

**a**[figure not shown]**b**[figure not shown]

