### 8.3.3 *Exploratory Endpoints*

#### *Translational Research*

- For a detailed workplan of translational studies see **Appendix A**,
- The analysis of these data will be performed with a prospective exploratory intent. No formal hypotheses testing is planned,
- Characterize the pharmacokinetic profile of SGI-110 and decitabine. For a detailed workplan of pharmacokinetic analyses see **Appendix B**.

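### Supplementary Figure 8b tests ICR/GIE class against response in 6 versus 8 patients with Pearson's chi-squared, although some expected counts are below 5 for every possible class split (minor, exploratory)

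*Combined protocol and SAP*

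**What the plan says.** Panel b of Supplementary Figure 8 plots ICR score against GIE at baseline for R (n = 6) and NR (n = 8) patients, "and their proportion (right) after classification as ICR/GIE classes". The p-value is described as coming from a "two-sided Pearson's chi-squared test statistic". The legend mentions no continuity correction, exact test or permutation for this comparison. The total of 14 agrees with Supplementary Figure 1: "Overview of sample profiling and clinical information for N=14 patients of NIBIT-M4 trial".

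The readable text does not give the number of classes, the cell counts or the p-value. The figure is not shown, and the source data are in a separate file.

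On the status of the translational analyses, protocol section 8.3.3 says: "The analysis of these data will be performed with a prospective exploratory intent. No formal hypotheses testing is planned".

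**The concern.** Pearson's statistic follows a chi-squared distribution only approximately, and the approximation needs expected counts that are not small. A common rule of thumb asks for 5 or more. Fourteen patients split 6 to 8 cannot meet that rule in every cell, however they are classified. The true distribution of the statistic is then coarse, and the chi-squared tail can differ from it materially in either direction.

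What is at stake is whether the printed p-value can be taken at face value. Appendix A says that biological results will be correlated with clinical parameters to find correlates of outcome. A reader will use a p-value linking a baseline class to response in that way, even without a formal hypothesis behind it.

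**Working it through.** **Inputs.** R = 6, NR = 8 and total = 14 (Supplementary Figures 1 and 8b). The test is Pearson's chi-squared (Supplementary Figure 8b). The number and size of the classes are unknown, so all possible splits were examined. There is no stated p-value to reproduce.

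**Step 1: expected counts.** Expected count = row total × class total / 14. With k classes the smallest class holds at most 14/k patients, so the smallest expected count is at most 6 × (14/k) / 14 = 6/k. Since class totals are whole numbers:

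| Classes | Largest possible smallest class | Best smallest expected count | Fewest cells below 5 |
|---|---|---|---|
| 2 | 7 | 6 × 7/14 = 3.0 | 2 of 4 |
| 3 | 4 | 6 × 4/14 = 1.7 | 4 of 6 |
| 4 | 3 | 6 × 3/14 = 1.3 | 7 of 8 |

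No split avoids the problem.

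**Step 2: true size of a nominal 5% Pearson test.** With the class totals fixed, there are C(14,6) = 3,003 equally likely ways to label 6 of the 14 patients as R. The true size is the share of these arrangements for which uncorrected Pearson gives p < 0.05.

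Two classes, all seven splits:

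| Split | Arrangements with p < 0.05 | True size |
|---|---|---|
| 1/13 | 0 | 0% |
| 2/12 | 0 | 0% |
| 3/11 | 165 | 5.5% |
| 4/10 | 255 | 8.5% |
| 5/9 | 273 | 9.1% |
| 6/8 | 77 | 2.6% |
| 7/7 | 308 | 10.3% |

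Three classes (16 splits): 0% to 6.8%, with the maximum at 4, 5, 5. Four classes (23 splits): 0% to 9.3%, with the maximum at 2, 4, 4, 4. The size exceeds 5% in 4 of 7, 3 of 16 and 5 of 23 splits respectively, which is 12 of 46 in all.

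**Step 3: effect on individual p-values.** There are 61 two-class tables with these row totals and no empty class. In 22 of them Pearson p is below 0.05. In 8 of those 22, Fisher's exact p is 0.05 or more (0.055 to 0.103). In the other 14 both are below 0.05; for example, 6/6 versus 2/8 gives 0.005 and 0.010. With three classes, tables whose Pearson p rounds to 0.03 have an exact p of 0.019 to 0.043. With four classes the range is 0.010 to 0.032. The exact value can therefore lie on either side of Pearson's.

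**Step 4: illustration with assumed counts.** Suppose two classes of 7, with 5 of 6 R and 2 of 8 NR in one of them.
- Pearson: 14 × (5×6 − 1×2)² / (6×8×7×7) = 14 × 784 / 2,352 = 4.67, p = 0.031.
- With continuity correction: 14 × (28 − 7)² / 2,352 = 2.63, p = 0.105.
- Fisher: 2 × [C(7,5)×C(7,1) + C(7,6)×C(7,0)] / 3,003 = 2 × (147 + 7) / 3,003 = 0.103.

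**The case against.** The strongest reply is that section 8.3.3 makes these analyses exploratory with no formal testing, so no significance level or decision depends on this p-value. It is one panel of a supplementary figure, and Appendix A names neither ICR nor GIE among its planned assays. This stands, and it makes the point minor. It does not justify an unreliable reference distribution for a p-value that is printed.

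A second reply is that an exact test on so few patients is itself conservative. That is fair. In the 7/7 split only the two most extreme tables have a Fisher p below 0.05, so the true size is 2 × 7 / 3,003 = 0.5%. Still, an exact test holds its level, while Pearson's may overshoot or undershoot by an unknown amount.

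A reader might infer more than the documents support:
- **That the panel reports p = 0.03 where the exact value is 0.10.** No p-value or count is readable. That pair arises only from 5/6 versus 2/8 and its mirror image among two-class tables, and from no three- or four-class table.
- **That Pearson's p is generally too small.** With two classes it is below Fisher's in 60 of the 61 tables. Over all splits, however, the nominal 5% test exceeds its level in only 12 of 46, and with three or four classes the exact p is sometimes the smaller one.
- **That this is a leading correlate of the trial.** The documents do not rank the correlates.

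**Conclusion.** The concern holds as a minor point. With 6 and 8 patients, expected counts below 5 are unavoidable, so the chi-squared p-value for Supplementary Figure 8b is unreliable whatever the class counts. This rests only on the stated group sizes and the named test.

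The size and direction of the error for the actual data remain unknown until the class counts are read from the figure or the source data. The ranges above bound the behaviour of the test. They assume the uncorrected statistic, since the legend mentions no correction, and use 5% as a conventional yardstick, since the protocol sets no level for this analysis. The result may keep or lose nominal significance under an exact test, and the documents do not show which. The primary MTD and safety evaluation (section 8.3.1) is untouched.

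**What to change.** Replace Pearson's chi-squared in Supplementary Figure 8b with Fisher's exact test, or the Fisher-Freeman-Halton test if there are more than two ICR/GIE classes. Report the exact p-value and name the test in the legend. If the panel does not already show the number of R and NR patients in each class, add those counts so that a reader can reproduce the value.

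The cost is one line of code and a legend edit. The drawback is that the p-value may become less favourable, and in a sample this small an exact test has little power.

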## SYNOPSIS

### Clinical Protocol NIBIT-M4

**Title of Study:** A phase 1b study of SGI-110 in combination with ipilimumab in unresectable or metastatic melanoma patients

Estimated Number of Study Centers and Countries/Regions: 1 NIBIT Center in Italy

Study Phase: Ib

**Research Hypothesis:** The research hypothesis is that SGI-110 will be able to be safely administered in combination with ipilimumab in previously treated or untreated unresectable or metastatic melanoma patients. At the same time, preliminary signals of biological and clinical activity will be collected.

**Primary Objective:** To assess, Maximum Tolerated Dose (MTD) and safety of SGI-110 in combination with ipilimumab in 21 day cycles in melanoma patients.

#### Secondary Objectives:

To evaluate the immune-related (ir) -Disease Control Rate (ir-DCR), immune-related (ir) -Objective Response Rate (ir-ORR), immune-related (ir) -Time to Response (ir-TTR) and immune-related (ir) -Duration of Response (ir-DOR).

To evaluate median immune-related (ir) Progression Free Survival (ir-PFS), median Overall Survival (OS), and survival rate at 1 and 2-years.

#### Exploratory Objectives:

To investigate immune-biologic correlates to treatment with SGI-110 in combination with ipilimumab (see Appendix A)

Characterize the pharmacokinetic profile of SGI-110 and decitabine. For a detailed workplan of pharmacokinetic analyses (see Appendix B)

**Study Design:** This is a Phase 1, dose-escalation study aims to evaluate the safety, tolerability, and Maximum Tolerated Dose (MTD) of SGI-110 in combination with ipilimumab in unresectable or metastatic melanoma patients.

All patients will undergo eligibility assessments within 28 days prior to starting study treatment. Serial safety and tumor response assessments will be performed during the study, and patients will continue

taking study treatment until documented disease progression, intolerable toxicity, withdrawal of consent, discontinuation at the discretion of the investigator or premature termination of the study.

**Phase 1b, Dose Escalation:** 3+3 dose escalation design.

Dose escalation will be dependent on the available toxicity information (including adverse events that are not DLTs), PK, and efficacy information, as well as the recommendations from the scientific committee

The dose escalation of SGI-110 will follow a 3+3 design. Cohorts of 3-6 patients will receive a combination therapy of Ipilimumab 3mg/kg d 1 q21 and SGI-110 according to protocol. Each patient will receive SGI-110 s.c. for 5 consecutive days (D1-5) during a 3-week cycle at the one of following doses:

- Dose Level -1: 15 mg/m^2 day

- Dose Level 0: 30 mg/m^2 day

- Dose Level +1: 45 mg/m^2 day

- Dose Level +2: 60 mg/m^2 day

In the absence of dose-limiting toxicities (DLTs), the starting dose of SGI-110 of 30 mg/m^2 day (Dose Level 0) will be escalated to 45 mg/m^2 day on Days 1-5 (Dose Level +1). In the absence of DLT in level +1, the dose of SGI-110 of 45 mg/m^2 day will be escalated to 60 mg/m^2 day on Days 1-5 (Level +2). In the presence of 1 DLT in 3 subjects of the starting dose cohort (Dose Level 0), the cohort will enroll 3 more subjects at the same dose level. In the event that 2 or more DLTs were encountered at the starting dose cohort (Level 0), the next lower dose level of 15 mg/m^2 (Dose Level -1) will be evaluated.

The same for Dose Level +1: in the presence of 1 DLT in 3 subjects of the Dose Level +1, the cohort will enroll 3 more subjects at the same dose level. In the event that 2 or more DLTs were encountered at the Dose Level +1 cohort, the next lower dose level of 30 mg/m^2 (Dose Level 0) will be evaluated.

The MTD will be the highest SGI-110 Dose Level (15-60 mg/m^2 day on Days 1-5) in combination with ipilimumab at which no more than 1 of 6 experiences a DLT. Once the MTD is established, additional subjects will be treated at that dose up to a total of 19 subjects in the study. If no irDCR is observed the study may be terminated.

**Duration of Study:** We assume a planned uniform accrual period of 24 months and a follow-up period of 24 months.

Patients will be treated until Progressive Disease (PD), or confirmed PD, excessive toxicity, or patient refusal. All subjects discontinuing treatment will be followed with efficacy assessments until confirmed

PD and will be followed for survival until 2 years post Last Patient First Visit. The total study duration will be approximately 48 months.

**Number of Subjects per Group:** this is a Phase 1b, 3+3 dose escalation, study. Sample size will range from 6 to 19 patients.

**Study Population:** Subjects (men and women)  $\geq 18$  years old presenting with previously treated or untreated unresectable Stage III or Stage IV melanoma with measurable lesions by CT or MRI per WHO criteria, that can be amenable to biopsy. An ECOG Performance Status of 0 or 1 and adequate bone marrow, renal and liver functions are required at study entry.

